## Methods/Design

### Participants

First, 90 obese individuals are recruited via direct advertisement to the community in Sydney, Australia. Inclusion criteria are: BMI ≥30 kg/m^2^, age 18 to 55 years, current weight under 180 kg, ability to provide informed consent and having completed 10 years of education in English. Participants who are depressed, have a binge eating disorder, are currently on psychotropic medication, have hypertension (medicated or not medicated), type 2 diabetes, or high cholesterol are eligible. Participants are excluded if they have a history of psychosis, head injury, neurological disorder including degenerative or inflammatory conditions or stroke, attention deficit hyperactivity disorder, epilepsy, developmental or intellectual disability; are unable to complete the testing (e.g. due to hearing, vision or language impediment); are on regular sedative or stimulant medication; and/or report regular substance use or abuse (for alcohol, more than two standard drinks five times a week). Individuals are also be excluded if they regularly use sedatives, hypnotics, antipsychotics, or anti-cholinergic or cholinergic medication. The sample size of 45 per group has been determined based on power estimates using Cohen’s tables for an estimated effect size of 0.6, power of 0.8, one-tailed test, *P* <0.05 and attrition of 20%. Although there are no previous studies of adults with obesity, these levels are commensurate with those achieved by Verbeken *et al*. [12].

### Procedure

Recruitment was via advertisements placed on social media sites, university and community centre notice boards and via media interviews with journalists from metropolitan and community newspapers. The initial screen was by phone to establish potential eligibility. This was followed by a face-to-face psychological and neuropsychological assessment. All 90 participants then receive group-based BWLT that will run once a week for 3 weeks, each se**s**sion lasting 90 minutes. At the completion of the third and final session, participants are randomly allocated to CRT-O or no treatment. Randomisation and allocation concealment are conducted using an external computer-based program [31]. The RCT is registered with the Australian New Zealand Registry of Clinical Trials (trial id ACTRN12613000537752) (Figure 1).

**Figure 1 Fig1:**

**Trial flow.** BWLT, Behavioural Weight Loss Therapy; CRT-O, Cognitive-Remediation Therapy for Obesity.

### Assessment

After providing information on demographic and medical factors, including their weight, height, waist and hip circumferences, participants undergo a battery of neuropsychological and psychological tests. All assessment measures will be administered at baseline, after 7 to 9 weeks (3 weeks of BWLT and 4 to 6 weeks of either CRT or no treatment), and at the 3-month and 1-year post-CRT follow-ups. At the follow-ups, participants will also be asked whether they received any further treatment for their obesity. We will control for this in the final analyses.

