#### Eating disorder symptoms

Individuals with eating disorder symptoms, such as binge eating, may have more difficulty losing weight [59] and hence this will be controlled for in our analyses. Eating disorder symptoms are measured by the Eating Disorder Examination Questionnaire [60]. Acceptable internal consistency and test–retest reliability have been demonstrated for this questionnaire [61]. It has 36 items and measures concerns about shape, weight and eating; restraint and self-reported binge eating. Subscale scores for shape, weight and eating concerns and restraint range between 0 and 6. A higher score indicates more severe eating psychopathology.

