### Treatment fidelity

The first author (JR) was trained in a workshop on CRT-AN by the developers of this treatment approach ([name] and [name], Institute of Psychiatry, King’s College London, UK). The third author (ES) piloted the different versions of manualised CRT-O with three people. Concomitant interventions outside of the trial setting are neither encouraged nor prohibited during the intervention phase. To increase transparency and documentation as well as for quality and treatment fidelity assessment, 10% of the sessions will be audiotaped.

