### Data collection, management and analysis

Data is collected at baseline, end-of-treatment and the 3-month follow-up by the trial therapist. An independent assessment, blind to intervention group, will be made at the 1-year follow-up. Data is entered, cleaned and coded by a research assistant, blind to group allocation, and stored at a secure university facility according to university protocols. An independent statistician will conduct all preliminary analyses. The Statistical Package for Social Sciences (SPSS) statistics will be used.

Neuropsychological measures will first be examined independently and will then be integrated in an executive function composite following the procedure recommended by Rosnow and Rosenthal [79, 80] and applied by Clark *et al*. [81]. The composite score will be generated by converting each executive function scale across all assessment points to *z*- scores, and then averaging across the measures.

Descriptive statistics will be used to present demographic and clinical data including eating disorder features. Baseline univariate between-group tests will be used to compare outcome variables and clinical and demographic data for the groups. Data will be analysed following the intention-to-treat principle. Linear mixed effects modelling [82] will be used to test for between-group differences in the continuous outcome measures, namely the composite scores of cognitive function, waist circumference and BMI, and potential confounds (e.g., levels of depression, anxiety, stress and emotion dysregulation). Generalised estimating equations [83] with a logit response function, or logistic regression, will be used for dichotomous outcomes, such as achieving a 5% reduction in body weight. Effect sizes between and within the two groups will be calculated with Cohen’s *d* computed with the pooled standard deviation, and the odds ratio will be presented where appropriate.

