The strengths of our study design include adequate concealment of randomised group allocation, use of validated and standardised assessments, and independent blinded data analysis. A limitation is that follow-up assessments are blinded only at 1 year. However, this is an important outcome time, since to be clinically meaningful for longer-term weight-loss maintenance, improvements in cognition need to be sustained over time. Furthermore, the Institute of Medicine has defined criteria for assessing successful weight maintenance as a weight loss of ≥5% of body weight that is maintained for at least a year [84]. For the purposes of this study, the Institute of Medicine’s criteria will be used as a standard definition of successful weight maintenance at this study's 1-year follow-up. Another limitation is that therapeutic time with a therapist is not matched between conditions and participants are not blind to condition, i.e., we are not employing a control–therapy comparison. As obesity tends to get worse without treatment, at our 1-year follow-up, we will examine whether individuals’ BMI is significantly higher in the no-treatment group compared to the CRT-O group. We will also control for any additional treatment each group received in that time and whether the change of executive function predicted that weight loss.

The design of this RCT offers a pathway to address, for the first time, the integral aspects of executive function and its impact on obesity, and their interaction with other maintaining factors such as emotion dysregulation, depression and habitual cluster behaviours. It is hoped that the findings of this RCT will provide an important first step towards an understanding of the potential of CRT in obesity. Based on the limited success of current behavioural weight-loss programmes and coupled with the data on the executive function deficiencies in obesity, it appears likely that improving an individual’s executive function has the potential to enhance treatment outcomes for obesity.

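### The final analyses are to control for further obesity treatment received after randomisation, which does not estimate the intention-to-treat effect and is open to bias if uptake differs by arm

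*Protocol article*

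**What the plan says.** Under Procedure, allocation comes after the group programme: "At the completion of the third and final session, participants are randomly allocated to CRT-O or no treatment". Under Assessment, the information on later treatment is collected after that point: "At the follow-ups, participants will also be asked whether they received any further treatment for their obesity". The next sentence commits the analysis: "We will control for this in the final analyses". The Discussion, on the 1-year BMI comparison, makes the same commitment: "We will also control for any additional treatment each group received in that time". Neither sentence confines the adjustment to a sensitivity or exploratory analysis.

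Under Data collection, management and analysis the principle is given as "Data will be analysed following the intention-to-treat principle", and linear mixed effects models "will be used to test for between-group differences in the continuous outcome measures". Further treatment is not named in that section.

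Two other statements bear on whether uptake could depend on arm. Treatment fidelity says "Concomitant interventions outside of the trial setting are neither encouraged nor prohibited during the intervention phase". The Discussion acknowledges as a limitation that participants know their condition and that there is no comparison therapy.

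**The concern.** Adjusting for a variable measured before randomisation leaves the randomised comparison intact. Further treatment is different, because it is one of the things that can follow from allocation. A participant who knows that nothing more is on offer has more reason to look elsewhere. The Discussion itself expects obesity to worsen without treatment and plans to test for higher BMI in controls at 1 year. People who are doing badly may also seek help in either arm, so uptake can carry information on prognosis.

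Putting such a variable in the model does two things. It removes any part of the effect of assignment that runs through later treatment. It also compares arms within levels of uptake, where the people in the two arms need no longer be alike. At stake are the follow-up comparisons, including the 1-year visit, which is the only blinded assessment and the one that the Discussion stresses. A larger sample would not remove the distortion.

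**Working it through.** **1. The plan's own figure.** Inputs from Participants: effect size 0.6, power 0.8, one-tailed 5% test, attrition 20%. The t-based sample size is 35.04, so 36 per arm, and 36 / (1 - 0.20) = 45. The stated 45 per group is reproduced. The point does not alter it; 0.6 SD serves below only as a yardstick.

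**2. Order of events.** Randomisation is at the end of the third group session, and further treatment is asked about at the 3-month and 1-year follow-ups. The covariate is therefore post-randomisation.

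**3. When adjustment changes the answer.** Let A be arm (1 = CRT-O), M further treatment (1 = yes), and p_T and p_C the uptake in the CRT-O and control arms. In linear regression:

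effect of A without M = effect of A with M + β_M × (p_T - p_C)

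so shift (adjusted minus intention-to-treat) = β_M × (p_C - p_T).

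The shift is zero if uptake is equal, or if M is unrelated to outcome within arm (β_M = 0). β_M combines any true benefit of further treatment (pushing it up) with confounding by prognosis (pushing it down when people doing worse seek more help), so its sign is not known in advance.

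**4. Size under assumptions.** Model: Y = d·A + b·M + g·U + e. Y is in SD units with higher better, U is unmeasured prognosis with SD 1, e has variance 1 - g², and the log-odds of M fall by γ per SD of U. The direct effect is d = 0.6. There were 500,000 simulated participants per scenario. The uptake rates, b, g and γ are all assumptions; the article gives none of them.

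| Uptake, control vs CRT-O | b | g, γ | Intention-to-treat | Adjusted | Shift |
|---|---|---|---|---|---|
| 30% vs 30% | 0 or 0.3 | all settings | 0.598 to 0.605 | 0.599 to 0.604 | within 0.001 |
| 40% vs 20% | 0.3 | 0, 0 | 0.539 | 0.600 | +0.060 |
| 50% vs 20% | 0.3 | 0, 0 | 0.516 | 0.606 | +0.090 |
| 40% vs 20% | 0 | 0.5, 1 | 0.601 | 0.515 | -0.086 |
| 50% vs 20% | 0 | 0.5, 1 | 0.601 | 0.473 | -0.127 |
| 40% vs 20% | 0 | 0.7, 1.5 | 0.597 | 0.445 | -0.153 |
| 50% vs 20% | 0 | 0.7, 1.5 | 0.600 | 0.368 | -0.231 |
| 40% vs 20% | 0.3 | 0.5, 1 | 0.538 | 0.514 | -0.025 |
| 50% vs 20% | 0.3 | 0.7, 1.5 | 0.513 | 0.373 | -0.139 |

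Hand check of rows 2 and 3: intention-to-treat = 0.6 + 0.3 × (0.20 - 0.40) = 0.54, and 0.6 + 0.3 × (0.20 - 0.50) = 0.51. The adjusted value is 0.60, so the shifts are +0.06 and +0.09. With b = 0 and no link to prognosis, the shift was zero even with unequal uptake, as step 3 requires.

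**5. No true effect (d = 0, b = 0, M related to prognosis).** The adjusted estimates were -0.084, -0.128, -0.152 and -0.229 SD, where the intention-to-treat value is 0.

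**The case against.** **No evidence of differential uptake.** The article gives no uptake by arm, and with equal uptake nothing moves. This stands. The claim has to be that the estimate is open to bias, not that it is biased. A stated commitment to condition on the variable is still a poor choice when the design makes unequal uptake plausible.

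**Intention-to-treat may mean only that participants are analysed in the arm assigned.** On that reading a covariate breaches nothing, and the analysis section does not list further treatment in the model. The detail may sit in an analysis plan that is not shown. This softens the contradiction but does not remove it: the article says twice that the adjustment will be made, once for the final analyses without restriction.

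**The investigators may want the effect in the absence of further treatment.** That is a legitimate question, and rows 2 and 3 of the table show adjustment recovering the direct effect when uptake is unrelated to prognosis. A covariate does not identify that effect when uptake and outcome share causes, and the article states neither the estimand nor a method for handling such causes.

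**The primary outcome may be little affected.** The question is put only at the 3-month and 1-year follow-ups, so the end-of-treatment contrast is untouched unless further treatment enters as a person-level covariate across all visits, which is not stated. The scenarios are in generic SD units, and the article gives nothing that links outside obesity treatment to neuropsychological scores. This stands as a limit on scope.

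**Two stronger readings are not supported.**

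- A reader might infer that the adjustment inflates false claims of benefit. Take a spurious shift of 0.10 to 0.13 SD against CRT-O, inside the range in step 5. With 36 per arm the standard error is √(2/36) = 0.236, so the shift is 0.42 to 0.55 standard errors. A two-sided 5% test would then reject about 7.1% to 8.5% of the time, but Participants specifies a one-tailed test. For superiority of CRT-O its false-positive rate would fall to about 1.4% to 1.9%. In that scenario the risk is underestimation and lost power.
- A reader might extend the point to eating disorder symptoms, of which the article says "hence this will be controlled for in our analyses". Psychological assessment explains that these measures serve partly to check that the groups are equivalent at baseline, and the reason given for adjustment is prognostic. Baseline adjustment is the natural reading, and it is sound.

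**Conclusion.** The point holds as a stated analysis choice that does not match the stated principle. Controlling for further obesity treatment in the final between-group analyses does not estimate the effect of assignment and gives up the protection of randomisation for the contrasts where it is applied, mainly those at 3 months and 1 year.

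Under assumed uptake of 40% to 50% in controls and 20% with CRT-O, the shift runs from about +0.09 to -0.23 SD. The larger figure is 0.23 / 0.6 = 38% of the design effect. The shift is zero if uptake is equal. Neither its size nor its direction can be fixed from the article. That allocation changes uptake is a reasonable expectation from the unblinded no-treatment comparison, not something the article shows.

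**What to change.** Replace the two sentences, under Assessment and in the Discussion, with a statement along these lines: the main between-group models adjust only for covariates measured before randomisation and use all outcomes regardless of further treatment; further treatment is reported by arm at each follow-up; any analysis that accounts for it is labelled supplementary, with its own estimand and a method suited to that estimand. The choice of baseline covariates and of the supplementary method can be left to the analysis plan.

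The cost is wording only: no new data, no change to the 45 per group and no change to conduct. Trial status reports that data collection is still in progress, so the change can be made and dated before the final analyses.

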#### Neuropsychological assessment

The six neuropsychological tests employed are selected because they cover different aspects of executive functioning and are commonly used in clinical and research settings. The tests are administered individually to all subjects by a trained clinical psychologist or neuropsychologist.The Wisconsin Card Sorting Test (WCST) 64: The computerised version of WCST [32–34] will be used. In this test, subjects are instructed to categorise a series of cards according to one of three stimulus features (colour, shape or number of illustrations on them), without this principle being revealed to the subject. After each association, the only feedback given is whether a match is correct or incorrect, the idea being that subjects should infer how to categorise based on the feedback they receive. This test measures categorisation, inference, testing of hypotheses, cognitive flexibility, cognitive inhibition and response to feedback [16]. The number of total errors and perseverative errors and failure to maintain a set are the dependent measures. WCST is considered to be a valid measure of abstract reasoning ability to maintain an appropriate planning and problem-solving strategy across changing stimulus conditions to achieve a future goal, and it is the most widely used test of executive function [35].Digit Span, a subtest of the Wechsler Adult Intelligence Test III [36]: In this test, the subject is presented with a series of digits to be repeated in the same order (Digit Span Forward) followed by another series to be repeated backwards (Digit Span Backward). Digit Span Forward assesses the phonological loop and Digit Span Backward assesses central executive aspects of the verbal working memory [37]. The score is calculated based on the number of correct responses that could be immediately retained.Trail Making Test (TMT) [38]: This will be used to assess psychomotor speed, visual integration, cognitive flexibility and inhibitory control. This test measures the subject's ability to connect written numbers in an ascending order (Trail A), and, afterwards, to connect numbers and letters, alternating numbers in ascending order and letters in alphabetical order (Trail B), for example, 1-A-2-B. The score is the response time taken to complete the respective trails [35].Computerised Reward–Loss Task [39]: This is a probabilistic classification task that assesses decision-making. In each trial, participants view one of four images and are asked to guess whether it belongs to category A or B. In the reward-learning task, if the participant correctly guesses the category membership for a trial, a reward of +25 points is received. If the participant guesses incorrectly, no feedback is given. In the punishment-learning task, if the participant guesses incorrectly for a trial, a punishment of -25 points is received, and correct guesses receive no feedback. The reward and punishment trials are intermixed so that no-feedback trials are ambiguous. The ±25 points symbolise quarter dollars that are won or lost, but no real payments are used in this study. The dependent variables are the number of errors made and completion time.Behaviour Rating Inventory of Executive Function, Adult Version (BRIEF-A) [40]: This is a widely used, standardised measure based on a multidimensional model of executive function and the only available self-report measure of executive function at present. The BRIEF-A captures information on an adult’s executive functions or self-regulation in his or her everyday environment.Rey–Osterrieth Complex Figure Test [41, 42]: This test (both copy and a 3-minute recall) will be used to measure attention to detail (central coherence), perceptual and organisational skills, and nonverbal memory. Scores will be calculated for the copy and 3-minute delay portions of the test using the scoring manual.

#### Pre-morbid IQ

The Australian version of the National Adult Reading Test, Revised [43, 44] is administered to control for pre-morbid intelligence. This is a widely used reading test that provides an estimate of pre-morbid IQ. It consists of 50 irregularly spelled words, listed roughly in order of difficulty. The test involves participants being presented with a word card and instructed to read each word out aloud. Interviewers then record correct pronunciations, with the total number of correct responses being the score.

#### Anthropometric measures

For participants, we measure: (1) height and weight with calibrated scales (from which we will derive BMI in kg/m^2^), and (2) hip and waist circumferences to calculate the waist to hip ratio.

#### Demographics and medical history

Age, gender, education and socio-economic status (by postcode) are recorded in the general questionnaire. This form also includes medical history, current medical conditions and medication.

#### Nutrition and lifestyle behaviours

These are assessed using a written 24-hour dietary recall method [45]. A brief questionnaire examining basic food group frequencies and portion sizes, and a questionnaire on frequency and intensity of exercise are used, both adapted from large Australian population questionnaires in the Australian Women’s Health project [46] and the National Nutrition Survey, Australia [47].

### Psychological assessment

The Clinical Obesity Maintenance Model [48] proposed by Raman and colleagues argues that psychological variables, such as habitual cluster behaviours, emotional dysregulation and mood, interact with executive functioning and impact on the overeating and binge eating behaviours of obese individuals. Hence, the following measures are included in this RCT to investigate the broader range of maintaining mechanisms, including but not limited to executive deficits, and to ensure both groups are equivalent at baseline in other measures that may impact on weight.

#### Depression, Anxiety and Stress Scales

Depression symptoms in the obese in this study are measured by the 21-item Depression, Anxiety and Stress Scales [49]. Obesity has been shown to increase the risk of developing depression and depression has been found to be predictive of obesity [50], and there is a dose–response gradient in that the association between depression and obesity was stronger than the association between depression and being overweight [51]. There is ample evidence that depressive disorders are also associated with deficits in attentional functions, executive control and lowered cognitive flexibility [52]; verbal learning and memory [53] and interpretation biases [54–57]. This test has been validated in a number of clinical and non-clinical populations and is psychometrically sound with good reliability and validity to measure depressive symptoms [49, 58].

